## Abstract

*Background*: Dehydration may affect cognitive performances as water accounts for 75% of brain mass. The purpose of this study is to investigate the effects of dehydration and water supplementation on cognitive performances, and to explore the changes of brain structures and functions using MRI. *Methods and Analysis*: A double-blinded randomized controlled trial has been designed and will be implemented among 64 college students aged 18–23 years from Baoding, China. Subjects will be asked to restrict water for 36 h. The first morning urine will be collected and urine osmolality measured. The fasting blood samples will be collected and osmolality and copeptin will be measured. Three MRI sequences, including fMRI, ASL and 3D BRAVO will be taken to observe the changes of whole brain volume, ventricular volume, BOLD response and the cortex thickness. Cognitive performances and mood will be performed with software and questionnaires, respectively. Subjects in the water supplementation groups 1, 2, 3 will drink 200, 500 and 1000 mL of water, respectively, while subjects in the no water supplementation group will not drink any water. After 90 min, urine and blood samples, MRI scans, cognitive performances and mood will be performed. One-way ANOVA will be used to study the differences among groups. *Ethics and Dissemination*: The study protocol has been approved by the Peking University Institutional Review Committee. Ethical approval project identification code is IRB00001052-16071. Results will be published according to the CONSORT statement and will be reported in peer-reviewed journals.

## 1. Introduction

Water, which makes up about 60–70% of human body weight [1], participates in metabolism, maintains electrolyte balance, and has other functions. It is very important for humans to maintain the balance of water input and output. When the water input is less than the output, people may be dehydrated. Dehydration may lead to some adverse results such as decreased muscle endurance and strength [2], or increased chances of kidney stones and urinary tract infections [3]. Furthermore, dehydration may affect cognitive performances, as water accounts for 75% of brain mass [4].

A few investigators have studied the effects of dehydration on human cognitive performances. However, there have been no consistent results and conclusions. Some studies have shown that dehydration impaired the cognitive performances in the aspects of short-term memory [5], vigilance attention, choice reaction [6], or working memory [7]. Other studies presented contradictory findings [8,9]. Mild dehydration affected the visual vigilance and visual working memory response latency of men [7], but without substantially altering the key aspects of cognitive performances of women [10], which indicated that there exist differences between genders that need to be studied further. The studies mentioned above used heat-stress, intense exercise, diuretics, or fluid deprivation or combined them to induce a dehydrated status. However, heat stress [11] or exercise [12] could also affect cognitive performances, which makes it difficult to investigate the effect of dehydration alone. When referring to the effects of hydration induced by fluid restriction alone, some studies found changes of moods [13,14,15], but the cognitive performances were not affected. More studies are needed to investigate the effects of dehydration induced by fluids restriction on cognitive performances.

Several studies have investigated the effects of hydration on brain volume and other changes of brain, which also gave conflicting results. Duning et al. [16] analyzed three-dimensional data sets at three time points: (1) before (baseline) and (2) after water restriction for 16 h, and (3) 20 to 30 min after drinking (rehydration). They found that after water restriction for 16 h, the brain volume had a decrease of 0.55% when compared with the baseline, moreover, after rehydration, the volume of brain increased 0.72% when compared with the baseline. Kempton et al. [17] used 90-min physical exercise to induce dehydration, and the results showed that acute dehydration could lead to the ventricular expansion, but there was no change in the volume of the total brain, which was different with Duning’s study. Nakamura et al. [18] found that the brain volume significantly increased by about 0.36% between the dehydrated and rehydrated states, but did not change significantly during the dehydration interval. The research, which was conducted among 10 adolescents (half males and half females), demonstrated that the dehydration, induced by thermal exercise, led to a significantly stronger increase in blood-oxygen-level-dependent (BOLD) responses during an executive function task than the control condition [19]. In a study conducted among 15 healthy individuals, the results showed that the brain tissue fluid had an decrease of 1.63% after fluids restriction for 12 h [20]. The conclusions of the above-mentioned studies were different presumably due to the confounding factors such as the different methods to induce dehydration, the different volumes of water intake, and the different intervals after water supplementation, which needs more studies with appropriate study designs.

Studies about the effects of dehydration on cognitive performances and mood have not been much reported. In the status of dehydration, the changes of whole brain volume, ventricular volume, BOLD response, the thickness of the cortex observed using Magnetic Resonance Imaging (MRI), have not been explored in China. In addition, the effects of different volumes of water supplementation after dehydration on cognitive performances and mood have not been investigated in China.

Referring to the effects of dehydration on cognitive performances, there was only one study conducted in China, which was designed and implemented by our team. It was a randomized controlled trial conducted among 68 college students. The results showed that water supplementation of 400 mL could improve the adverse effects of hypohydration on cognitive performances (unpublished). However, the study only investigated males. The level of dehydration conducted before was mild, however, and moderate dehydration was not investigated. Moreover, the changes of brain structures and functions in dehydration and water supplementation by MRI have not been explored yet. Hence, we designed a randomized controlled trial to investigate the effects of dehydration after 36 h of water restriction and rehydration after water supplementation on cognitive performances and the changes of brain structures and functions in different hydration status among male and females in free-living conditions.

We hypothesize that dehydration has adverse effects on cognitive performances and mood. Dehydration will induce the decrease of whole brain volume and the increase of ventricular volume, the BOLD and the cortex thickness. After water supplementation, the cognitive performances and mood will be improved. There will be an increase in the whole brain volume and decreases in ventricular volume, BOLD, and the cortex thickness. Moreover, there will be significant differences in the effects of dehydration on aspects of cognitive performances, mood, and the structures and functions of the brain between males and females in dehydration and water supplementation.

The purposes of this study are, first, to evaluate the effects of dehydration induced by 36 h water deprivation on cognitive performances and mood. Second, to explore whether cognitive performances and mood will be improved after water supplementation. Third, to compare the changes of whole brain volume, ventricular volume, BOLD response and the thickness of the cortex using MRI between dehydration and rehydration. Fourth, to compare the differences between males and females. Finally, to provide more suggestions for the associations between water intake and cognitive performances, may offer more scientific basis to revise the adequate water intake for young adults.

## 2. Methods and Analysis

### 2.1. Sample Selected

Subjects will be recruited using both online and campus recruitment advertisements among young adults from Hebei University Health Science Center, which is located in Baoding, China. All subjects will sign the informed consent form before participating the study. Anyone aged <18 years or >23 years or smoke, has habitual alcohol (>20 g/day) consumption or habitual high caffeine (>250 mg/day) consumption or intensive physical exercise, or has a chronic diseases or claustrophobia or any other neurologic, medical illness will be excluded from participation. Subjects will be instructed not to participate in strenuous activities, to maintain a normal diet and to avoid alcohol consumption during the 24 h before.

### 2.2. Sample Size Calculation

In a related study, the letter cancellation scores of subjects in the water group before and after water supplementation were 23.34 and 28.81, respectively [21]. According to the SAS procedures (SAS Institute Inc., Cary, NC, USA), with the power set at 0.8 and α set at 0.05, in addition, a 10% drop-out rate will be taken into account, so a total of 64 subjects will be needed, including half males and half females.

### 2.3. Ethics and Dissemination

All subjects will give their informed consent for inclusion before they participate in the study. The study will be conducted in accordance with the Declaration of Helsinki, and the protocol has been approved by the Peking University Institutional Review Committee. Ethical approval project identification code is IRB00001052-16071.

### 2.4. Study Design

A randomized controlled trial study design, which is double-blinded, will be employed. All recruited subjects will fast overnight for 12 h, without consuming any food or drink. They will be asked to have the meals provided by the study. Subjects will be randomly assigned into four groups using a random number generated by computer software: the water supplementation group 1, 2, 3 (WS group 1, 2, 3) with 200 mL (WS group 1), 500 mL (WS group 2) and 1000 mL (WS group 3) water, respectively and the no water supplementation group (NW group). The present study will assess cognitive performances, mood, subjective sensation of satiety, hunger, sleepiness and thirst during the experimental design three times. Moreover, MRI scans will be used to explore the changes of brain structures and functions for three times. In addition, measurements of weight, waist circumference, body composition, blood pressure, blood glucose, urine osmolality, urine specific gravity, plasma osmolality, and plasma copeptin will be executed at the same time. The study design is shown in Figure 1. All items from the World Health Organization Trial Registration Data Set are shown in Table 1.

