### 2.22. Statistical Analyses

Statistical analyses will be conducted using SAS 9.2 (SAS Institute Inc., Cary, NC, USA). One-way ANOVA or Kruskal-Wallis *H* test measurements will be used to investigate the effect of hydration statuses on the changes in urine indexes, plasma indexes, mood, cognitive performances and MRI scans among the four groups. The MRI data will be analyzed by professional analyst using MATLAB (Mathworks Inc., Natick, MA, USA) and SIENA (FMRIB Software Library, Oxford, UK). Two-sided significance levels will be set at 0.05 (*p* < 0.05) with 95% confidence intervals (95% CI).

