**Figure 2 ijerph-15-01477-f002:**
[figure not shown]
The study procedure (Note: H (Height); W (Weight); WC (Waist circumference); BP (Blood pressure); BG (Blood glucose); BC (Body composition); CP (Cognitive performances); POMS (Profile of Mood States); VAS (Visual Analogue Scales); MRI (Magnetic resonance imaging)).

**Table 1 ijerph-15-01477-t001:** All items from the World Health Organization Trial Registration Data Set (SPIRIT checklist, item 2b).

Data Category	Information
Registration number	ChiCTR-IOR-17011568 Chinese clinical trial registry
Registration State	1008001 Prospective registration
Public title	The effect of hydration and water supplementation on the cognitive performance of college students
Scientific title	Effect of Different Hydration State on Cognitive Performance
Approval of ethic committee	Peking University Institutional Review Committee
Ethical approval project identification code	IRB00001052-16071
Date of approved by ethic committee	5 December 2017
Study type	Interventional study
Study design	Randomized controlled trial
Key inclusion and exclusion criteria	Inclusion criteria: Aged between 18 and 23; Male and Female; In health state, without metabolic disease, oral diseases, and so on. Exclusion criteria: Aged < 18, or age > 23; With metabolic disease, oral diseases, and other diseases.
Interventions	Water supplementation
Outcomes	Urine osmolality, Blood pressure, Mood, Thirsty, Cognitive performances, MRI scans
Collecting samples	Urine, Blood
Recruitment state	Started
Randomization Procedure (please state who generates the random number sequence and by what method)	Primary sponsor generates random sequence with random number table

**Table 2 ijerph-15-01477-t002:** The schedule of enrolment, interventions, and assessments.

Timepoint	Enrolment	Allocation	Post-Allocation	Close-Out
	5 April 2018	10 April 2018	15 April 2018	30 May 2018
Enrollment:				
Eligibility screen	X			
Informed consent	X			
Allocation		X		
Interventions:				
Water supplementation			X	
Assessments:				
Baseline anthropometric measurements variables: height, weight, waist circumference, blood pressure, blood glucose, body composition	X		X	
Outcome variables: cognitive performances, mood, subjective sensation, MRI			X	X

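### Comparing males with females is a stated purpose and hypothesis, but the only stated analysis is one-way across arms, with no sex or sex-by-arm term, and no stratification by sex is described

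*Protocol article*

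**What the plan says.** **Purpose and hypothesis.** The Introduction lists among the purposes: "Fourth, to compare the differences between males and females". Its hypothesis paragraph expects significant differences in cognition, mood and the "structures and functions of the brain between males and females in dehydration and water supplementation". Because it concerns how far the effects differ by sex, it is a claim about interaction. The Discussion (section 4) names the evaluation of gender differences among the strengths, without a method.

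**Sample.** Section 2.2 concludes "so a total of 64 subjects will be needed, including half males and half females". This is an overall quota of 32 and 32. The article states no number per arm or per sex within arm.

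**Allocation.** Section 2.4 says "Subjects will be randomly assigned into four groups using a random number generated by computer software", and section 2.5 says the same in similar words. Table 1 gives a different source: "Primary sponsor generates random sequence with random number table". None of the three mentions sex, strata or blocks.

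**Analysis.** The abstract and section 2.22 name one-way ANOVA, with Kruskal-Wallis as the alternative in 2.22, to compare urine, plasma, mood, cognition and MRI outcomes among the four groups. Arm is the only factor in either method.

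**The concern.** The article commits itself to a hypothesis and to a model, and the two do not match. A one-way ANOVA on arm estimates four arm means averaged over sex. It cannot show whether the response to water differs between males and females, and it does not compare the sexes at all. Kruskal-Wallis has the same limit. If section 2.22 is followed as written, the fourth purpose goes unanswered, or it is answered by a test chosen after the data are seen.

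Allocation matters in a smaller way. The design expects about 8 subjects per sex per arm. The Introduction itself cites evidence that dehydration affects the cognition of men and women differently, so by the article's own account sex is related to outcome. Leaving its spread across arms to chance would lose precision that could be had at no cost.

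**Working it through.** **1. Promise against model.** The hypothesis needs a sex-by-arm term for the water phase and a sex-by-time term for the dehydration phase. Section 2.22 supplies the arm factor only. No arithmetic is needed: the term that carries the hypothesis is absent.

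**2. Does the sample size cover the sex comparison?** Section 2.2 gives a before–after change of 28.81 − 23.34 = 5.47 in one water group, "with the power set at 0.8 and α set at 0.05", and 10% drop-out. It gives no SD, so 64 cannot be reproduced without assuming one. With the two-sample formula per arm, four arms and division by 0.9:

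| Assumed SD | n per arm | Four arms | After 10% drop-out |
|---|---|---|---|
| 4 | 9 | 36 | 40 |
| 5 | 14 | 56 | 63 |
| 6 | 19 | 76 | 85 |
| 10 | 53 | 212 | 236 |

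An SD near 5 comes close to 64. None of these inputs describes a sex difference, so the 64 was not sized for one.

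**3. Sex within arms if allocation is not stratified.** Inputs: 32 males, 32 females, four arms. Equal allocation is assumed, as no ratio is stated.

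*(a) Arms fixed at 16, sex ignored.* The number of males in one arm is hypergeometric (16 drawn from 64, of whom 32 are male).
- One given arm 5:11 or worse: 2 × P(X ≤ 5) = 14.8%.
- Some arm 5:11 or worse: 42%.
- Some arm 4:12 or worse: 14%.
- All four arms exactly 8:8: C(16,8)⁴ / C(64,32) = 1.5%.

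*(b) Simple randomisation, probability 1/4 per arm (simulated).*
- Some sex-by-arm cell with 4 or fewer: 47%.
- Some cell with 3 or fewer: 19%.
- Some cell with 2 or fewer: 5%.
- Some cell empty: 0.08%.

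*Cost in precision.* Compared with 8 in every cell, the summed variance of the eight cell means rises by a median of about 4% under (a) (95th percentile about 14%) and about 10% under (b) (95th percentile about 33%).

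**4. Power of the interaction once it is in the model.** Completers: 64 × 0.9 = 57.6, taken as 58, or 8 × 0.9 ≈ 7 per cell. The level is as in section 2.22: "Two-sided significance levels will be set at 0.05".
- The arm effect detectable at 80% power (F with 3 and 54 df) is f = 0.45. The interaction (3 and 50 df) also needs f = 0.45.
- Suppose the sex difference in the group effect is as large as the average group effect. Each sex then departs from the average by half of it, so the interaction f is 0.45/2. The noncentrality is 58 × (0.4496/2)² = 2.93, and power is 25%.
- If the sex difference is half as large, the noncentrality is 58 × (0.4496/4)² = 0.73, and power is 9%.
- Cross-check with a two-arm difference in differences, 7 per cell: the two-arm effect detectable with 14 v 14 is (1.96 + 0.84) × √(2/14) = 1.06 SD. The standard error of the contrast is √(4/7) = 0.756 SD. Power is Φ(1.06/0.756 − 1.96) = 29%, or 10% if the sex difference is half as large.

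**The case against.** The case on the other side has several parts, and a good deal of it stands.

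- **Randomisation.** A reader might infer that randomisation ignores sex. The documents do not say so. Three descriptions are silent on strata and blocks, in a condensed article whose design figure is not shown, and the overall sex quota would be compatible with separate lists by sex. The probabilities above are therefore conditional on unstratified allocation.
- **Testing.** A reader might infer that sex differences will never be tested. The Discussion promises an evaluation, and an analysis plan that is not shown may specify one. What can be said is that no test is stated. This does not remove the point, because the article does state a model, and that model leaves sex out.
- **Size of the harm.** A reader might infer that chance could make the sex-by-water comparison unusable. An empty cell has probability 0.08% and a cell of 2 or fewer 5%, even under simple randomisation. The typical loss is a few per cent of precision, and adjusting for sex in the model deals with chance imbalance in the arm comparison.
- **Dehydration phase.** The male–female contrast before water is given uses all subjects, 32 v 32, so arm allocation cannot unbalance it.
- **Relative volume.** A reader might object that fixed volumes mix sex with volume per kg. A sex difference in response to a fixed volume is a legitimate question. Volume per kg is zero for everyone in the no-water arm and nearly collinear with arm elsewhere, so adjusting for it answers a different question and is not recommended.

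**Conclusion.** The point holds in this form: the male–female comparison is a purpose, a hypothesis and a claimed strength, and the stated analysis contains no term that could test it. This part rests on the text alone and needs no assumption.

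The allocation part is secondary and conditional. If allocation is unstratified, some arm is split 5:11 or worse in 42% of allocations with arms of 16, and some sex-by-arm cell has 4 or fewer in 47% under simple randomisation. The consequence is a modest loss of precision in the arm and sex-by-water comparisons.

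The tighter limit is sample size. With about 7 completers per cell, interaction power is about 25% under a generous assumption and about 9–10% if the sex difference is half as large. Correcting the model makes the hypothesis testable but not well powered.

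**What to change.** 1. In section 2.22 and the abstract, replace the one-way model with one containing arm, sex and sex-by-arm, and add sex-by-time for the dehydration phase. Kruskal-Wallis cannot carry these terms, so state what replaces it if the model assumptions fail.
2. In sections 2.4 and 2.5, state that allocation is made within sex in permuted blocks, giving 8 per sex per arm. If stratification was already planned, it is enough to say so.
3. Make Table 1 and sections 2.4 and 2.5 name the same source for the random sequence. At present one names a random number table and the others computer software.
4. Label the sex-by-arm comparison exploratory, report it with confidence intervals, and say that 64 was not chosen to detect it.

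The cost is a new allocation list, a few model degrees of freedom (one for sex and three for sex-by-arm) and a more modest claim about sex differences. No extra subjects or measurements are needed. Table 1 shows that recruitment has begun. If allocation has already been made, item 2 becomes a matter of reporting what was done, and items 1, 3 and 4 remain available.

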### 2.5. Randomization and Blinding

This will be a randomized double-blinded study, and subjects will be randomly assigned into different groups using a random number generated by the computer software. The assignment will be stored in numbered, sealed, opaque envelopes, which will be prepared by an investigator, who is not involved in assessments and subject recruitment. The envelopes will be opened by the investigator. The investigators who will complete the statistical analysis will be blinded to the data collection and data entry, with each subject identified by a random number. Moreover, when taking water supplementation, every subject will be given three opaque cups. The water supplied to the subjects in water supplementation will be contained in the three opaque cups, and subjects will be told to drink the water from the little hole on the cover of the cup within 10 min. After water supplementation, they are not allowed to talk with each other about the interventions they have had.

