Period 3: from 8:00 a.m. of the third study day to 10:35 a.m. of the third study day. Subjects will have water supplementation. They will be asked to arrive at the lab at 8:00 a.m. Measurements including weight, body composition, blood pressure, blood glucose and blood samples will be obtained as before. The first morning urine and blood samples will also be collected and tested. MRI scans, cognitive performances, mood and subjective sensation of the subjects will be performed. At 8:30 a.m., subjects in WS group 1, WS group 2, WS group 3 will be asked to drink 200, 500, and 1000 mL of purified water, respectively. The subjects in NW group will drink no water or other fluids. All the water will be offered in opaque containers which should be drunk within 10 min. All the water will be kept in 30 °C~40 °C to reduce the gastrointestinal discomfort of the subjects. During the interval of 90 min, all subjects will be asked to undertake normal activities in the room adjacent to the testing room. After water supplementation for 90 min (at 10:15 a.m.), weight, body composition, blood pressure and blood glucose will be measured. Urine and blood samples will be collected, stored and tested. MRI scans, cognitive performances, mood and subjective sensation will be measured again. The study procedure is shown in Figure 2.

Subjects will be asked everyday if they have fever, diarrhea or other illness during the study. During the three periods of the study, all subjects will not be allowed to undertake strenuous activities. After water supplementation, the gastrointestinal distress questionnaire will be conducted among the subjects to evaluate the discomfort.

The schedule of enrolment, interventions, and assessments is shown in Table 2.

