The present study has both strengths and weaknesses. First, a randomized controlled trial, which also is a blind designed study, will be conducted to reduce the bias, such as reporting bias, exposure suspicion bias and diagnostic suspicion bias. The investigators who conduct the measurements and the data analysts will be blinded to the intervention assignments. Secondly, the urine specific gravity, osmolality, and plasma osmolality will provide sufficient power to confirm the hydration statuses of the subjects. Blood urea nitrogen and creatinine will be measured during the dehydration in order to monitor the renal functions of the subjects. Third, the sample size will provide sufficient power to detect the effects. Finally, differences between genders will be evaluated.

In terms of the weaknesses, the effects of long-term water supplementation on cognitive performances will not be studied; more aspects of brain changes will not be explored; and the effects of different temperatures of water will not be investigated.

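### Subjects cannot be blind to water versus no water, so the double-blind label and the reporting-bias claim do not hold for self-rated mood and sensation

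*Protocol article*

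**What the plan says.** The abstract and two design sections of the protocol article call the trial double-blind. Section 2.4 says: "A randomized controlled trial study design, which is double-blinded, will be employed". Section 2.5 says: "This will be a randomized double-blinded study, and subjects will be randomly assigned into different groups".

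Section 2.5 gives two devices for masking subjects. The first is that "every subject will be given three opaque cups", with lids and a small drinking hole. The second is a ban on discussion: "After water supplementation, they are not allowed to talk with each other about the interventions they have had".

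Section 2.6 (Period 3) sets out what each arm does at 8:30 a.m. on the third study day. The three water arms "will be asked to drink 200, 500, and 1000 mL of purified water, respectively", within 10 minutes. For the control arm: "The subjects in NW group will drink no water or other fluids".

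Section 4 lists blinding as a strength: "First, a randomized controlled trial, which also is a blind designed study, will be conducted to reduce the bias, such as reporting bias". It adds exposure-suspicion and diagnostic-suspicion bias. Its next sentence says who is blinded: the investigators who take the measurements and the data analysts. Subjects are not on that list.

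On allocation, section 2.5 says that sealed opaque envelopes are prepared by an investigator with no part in assessment or recruitment, and then: "The envelopes will be opened by the investigator". It does not say when. Table 2 dates allocation 10 April 2018 and the post-allocation stage 15 April 2018.

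**The concern.** Double-blind is normally read to mean that subjects do not know their arm. Here one arm drinks nothing after a 36 h water restriction and the other three drink. Opaque cups hide water from sight. They do not hide whether a person has swallowed any.

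This matters most for outcomes that subjects rate themselves. The VAS for satiety, hunger, sleepiness and thirst is a mark made by the subject (section 2.10), and the POMS is a mood inventory (section 2.11). Both are repeated after the water (section 2.6). Better mood after water is a stated hypothesis and purpose (section 1). If the label stands, a difference in mood or thirst between the water and no-water arms would be presented as double-blind evidence when the subject's own knowledge and expectation could have contributed to it.

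A lesser matter is the time of allocation. The arms differ only from 8:30 a.m. on day 3, so nobody needs to know an assignment during the measurements before the water. The article does not say that it stays concealed until then.

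**Working it through.** The article gives no figure for blinding that could be reproduced, so the check sets its statements side by side.

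**Step 1: can each contrast be hidden from the subject?**

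Inputs: 0, 200, 500 and 1000 mL (section 2.6), drunk within 10 minutes from three opaque lidded cups (section 2.5).

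The split over the cups is not stated. Assuming an equal split, volume per cup = total / 3:

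| Arm | Total (mL) | Per cup (mL) |
|---|---|---|
| NW | 0 | 0 |
| WS group 1 | 200 | 200/3 ≈ 67 |
| WS group 2 | 500 | 500/3 ≈ 167 |
| WS group 3 | 1000 | 1000/3 ≈ 333 |

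- NW versus any WS group: something is drunk or nothing is. This cannot be masked without a sham drink. None is described, and the stated rule for the NW group excludes any fluid. Handing out empty cups would not change that.
- WS group 1 versus WS group 3: 1000/200 = 5. The total drunk differs five-fold, so the subject is likely to notice. This is an inference, but a strong one.
- WS group 1 versus 2: 500/200 = 2.5. WS group 2 versus 3: 1000/500 = 2. Masking may work in part here, since the article does not say whether subjects are told the possible volumes.

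**Step 2: whose blinding protects which outcome?**

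| Outcome | Who produces the value | Protected by blinding measurers and analysts? |
|---|---|---|
| VAS (four sensations) | the subject | No, not from the subject's own knowledge |
| POMS | the subject's account of mood | No, same reason |
| Urine, blood, MRI | instruments, technicians, analysts | Largely; much less exposed to reporting bias |

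Section 4 names reporting bias first among the biases reduced. For VAS and POMS the blinding it then lists cannot deliver that.

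**Step 3: how much of the trial is affected?**

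Table 1 lists six outcomes: urine osmolality, blood pressure, mood, thirst, cognitive performance and MRI. Two of them, mood and thirst, are self-reports (2/6 = one third of the listed outcomes).

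**Step 4: when is the assignment known?**

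Table 2 places allocation (10 April) before the post-allocation stage (15 April), which is one of the columns in which the outcome measurements are marked. Section 2.5 gives no time for opening the envelopes. Knowledge of the arm during the day-3 pre-water measurements is therefore neither stated nor ruled out.

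**The case against.** The best defence is that a comparison of drinking with not drinking can hardly be blinded for the subject. On that view the fault is one word in the design sections and one sentence in the Discussion, and correcting them changes no data or analysis. The plan also makes a real effort: identical opaque cups, a ban on discussion, and a statement of exactly who is blinded. All of this is fair. It limits how serious the point is, but it does not make the label true, and no later analysis plan could make the subjects blind.

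There are stronger readings that a reader might infer but that the article does not support:

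- *That blinding gives no protection at all.* The stated blinding of measurers and analysts can still guard against observer and analyst bias, including the exposure-suspicion and diagnostic-suspicion bias named in section 4. Neighbouring volumes may be partly masked.
- *That envelope opening contradicts the blinding of measurers.* The words "The envelopes will be opened by the investigator" directly follow the sentence on the preparer who takes no part in assessment. The natural reading is that they mean that person. The wording is at most ambiguous.
- *That arms are known before the water.* Table 2 gives one calendar date per stage. The allocation date fits generating and sealing the sequence as well as it fits unsealing it.
- *That the planned drop-out falls mainly in the restriction phase.* Section 2.2 gives a 10% rate (0.10 × 64 = 6.4 subjects) with no timing. Section 4 names lying still in the scanner as a challenge too, and one scan follows the water.
- *That most outcomes are compromised.* Counting seven POMS subscales and four VAS items against six cognitive tests and four MRI measures gives 11 of 21. That denominator leaves out the urine, blood and blood pressure outcomes.

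**Conclusion.** The point holds in a bounded form. The article claims a property, subject blinding, that its own procedure excludes for water versus no water and makes unlikely for 200 versus 1000 mL. The claim to reduce reporting bias therefore fails for POMS and VAS, which include two of the six outcomes in Table 1. It does not follow that the urine, blood or MRI results are biased, or that assessor blinding is broken.

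The conclusion on water versus no water needs no assumption beyond the absence of a sham drink from the described procedure. The conclusion on 200 versus 1000 mL assumes that people notice a five-fold difference in the amount swallowed. No size of bias in mood or thirst can be derived from the article, and none is claimed.

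The timing of envelope opening is a secondary gap: unspecified, not shown to be wrong.

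**What to change.** 1. In the abstract and sections 2.4 and 2.5, replace the double-blind label with a description of the trial as blinded for outcome assessors and data analysts, with subjects not blinded.
2. In section 4, withdraw the reporting-bias claim for POMS and VAS, and keep the claim about measurers and analysts. Add subject unblinding to the weaknesses.
3. Interpret and report POMS and VAS comparisons as open-label results.
4. As a secondary step, state in section 2.5 that each envelope is opened only after that subject's day-3 pre-water measurements are complete, by the investigator already named there as having no part in assessments. This keeps those measurements free of knowledge of the arm.

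Items 1 to 3 cost only wording, though the stated design will look less rigorous. Item 4 is a small change in logistics on the morning of day 3, between the 8:00 a.m. measurements and the 8:30 a.m. water. Arms, volumes, sample size and statistical tests stay as they are.
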